***SPIRIT Guidance:***

*11d Relevant concomitant care and interventions that are permitted or prohibited during the trial*

The site physicians are responsible to exercise their clinical judgement in provision of best diagnostic and therapeutic care to enrolled patients beyond this protocol, and record each/any of those within patient file and electronic data entry module.

***SPIRIT Guidance: Outcomes***

*12 Primary, secondary, and other outcomes, including the specific measurement variable (eg, systolic blood pressure), analysis metric (eg, change from baseline, final value, time to event), method of aggregation (eg, median, proportion), and time point for each outcome. Explanation of the clinical relevance of chosen efficacy and harm outcomes is strongly recommended*

Investigators will ensure collection of nasopharyngeal and oropharyngeal swab samples from participants at Days 7 and 14 (those positive at day 7 will be followed up further till day 14 or beyond) for monitoring of primary endpoint - measuring time to turn test negative for COVID-19 on qRT-PCR (Quantitative Reverse Transcription PCR). Swab samples will be taken by a trained ENT (ear-nose-throat) nurse as per local guidelines and sent to laboratory as per biosafety protocol **(attached)**. The clinical progression or recession in symptoms would be monitored and reported on the 7-point ordinal scale on each of days 3, 5, 7, 9, 11, and 14. For hospitalized participants, baseline investigations such as CBC, Urea electrolytes, kidney (Creatinine), liver (Liver Function Tests), and cardiac functions (Enzymes, D-dimers, ECG) are to be recorded preferably at the time of admission to hospital and as frequently as permissible within given resources. All participants should have undergone these investigations at least once during the recruiting period. Diagnostics such as Electrocardiogram, Hepatotoxicity, Nephrotoxicity, Myelotoxicity are indicated immediately upon suspected ADR as explained on Page 8 (Methods). It has to be mentioned that clinical and diagnostic facilities for Covid-19 vary across study sites due to administrative and geographical factors known to shape emergency responses.

Secondary outcomes like Quality of Life and Symptoms Score will be recorded on day 0 and 7 using standardized tools such as World Health Organization Quality of Life Questionnaire (WHO QoL) and Wisconsin Upper Respiratory Symptoms Survey (WURSS) respectively (copies **attached)**. The former is expected to capture participant’s lived experience during care that has not been documented in literature to date. The latter is expected to indicate any respiratory co-infection including those acquired from the hospital. The investigators will also monitor and record variables including duration it takes to oxygenate and ventilate, duration stayed oxygenated and ventilate, number of hospitals stay days, admission to intensive care, and mortality. This methodology has been peer reviewed by an external expert **(see annex 1).** A GCP certified, experienced researcher will conduct the training of up to 50 investigators across 13 participating sites to prepare them for all aspects of this study.

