**Abstract**

Objectives

To evaluate the effectiveness of Hydroxychloroquine Phosphate/Sulfate (200 mg orally 8 hourly thrice a day for 5 days) *versus* oseltamivir (75 mg orally twice a day for 5 days) *versus* Azithromycin (500 mg orally daily on day 1, followed by 250 mg orally twice a day on days 2-5) alone and in combination (in all seven groups), in clearing the coronavirus (COVID-19) nucleic acid from throat and nasal swab and in bringing about clinical improvement on day 7 of follow-up (primary outcomes).

Trial Design

An adaptive design, set within a comprehensive cohort study, is chosen because it permits flexibility in this fast-changing clinical and public health scenario. The randomized study will be a multicenter, multiarm, multistage, randomized controlled trial with a parallel design. An observation only cohort will emerge from those not consenting to randomization.

Participants

Eligible will be newly diagnosed patients, either hospitalized or in self-isolation, without any comorbidities or with controlled chronic medical conditions like diabetes mellitus and hypertension. Participants of any gender or age group having tested positive for COVID-19 on Real-Time qRT-PCR (Quantitative Reverse Transcription PCR) will be invited to take part in study at twelve centers across nine cities in Pakistan. Those pregnant or lactating, severely dyspneic or under respiratory distress, already taking a treatment, and with serious co-morbidities like liver or kidney failure will be excluded.

Intervention and Comparator

A total of seven comparator groups will be formed: Each drug (Hydroxychloroquine Phosphate/Sulfate, Oseltamivir and Azithromycin) given as monotherapy (three groups); combinations of each of two drugs (three groups); and a final group on triple drug regimen.

Main Outcomes

The laboratory-based primary outcome will be turning test negative for COVID-19 on qRT-PCR on day 7 of follow-up. The clinical primary outcome will be improvement from baseline of two points on a seven-category ordinal scale on day 7 of follow-up.

Randomization

Participants will be randomized, maintaining concealment of allocation sequence, using a computer-generated random number list of variable block size into multiple intervention groups.

Blinding

Computerized allocation to treatment group will be done upon adding participants demographic details and confirmation of informed consent. Neither physician nor participants will be blinded.

Sample Size

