***SPIRIT Guidance: Sample size***

*14 Estimated number of participants needed to achieve study objectives and how it was determined, including clinical and statistical assumptions supporting any sample size calculations*

This is an adaptive design and parameters for formal sample size calculation in a new disease of a previously unknown virus are not available. Then the sample size and power analysis are indicative for review at each stage of adaptive design. In a standard two-arm, head-to-head trial, the sample size would have been as follows: in order to detect a difference in the laboratory-based primary outcome of 10% (assuming a 50% of participants receiving Hydroxychloroquine Phosphate/Sulfate turn test negative at day 7 and expected rates in comparator groups of 60%), at a significance level 5% and a power of 90%, a sample size of approximately 520 subjects in each group will be required. This sample size will be enough to detect a small-medium difference (Cohen’s d 0.3, a significance level 5% and a power of 90%) in the clinical primary outcome. Additional considerations will need to make for the interim analysis at every stage of the adaptive design. Interim analysis will review sample size according to time to clearance also. Planned blinded sample size re-estimations will need to be undertaken in which we will constantly re-examine the original sample size assumptions. We will aim to maintain the trial power at 90% even if the original sample size assumptions turn out to be far from the observed data. The adaptation at each stage will allow us to drop out fewer promising interventions and will prevent an underpowered trial for the most promising interventions. As the planned modifications will be undertaken in a blinded fashion, there will be no increase in the type I error rate.

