***SPIRIT Guidance: Statistical methods***

*20a Statistical methods for analyzing primary and secondary outcomes. Reference to where other details of the statistical analysis plan can be found, if not in the protocol*

*20b Methods for any additional analyses (eg, subgroup and adjusted analyses)*

*20c Definition of analysis population relating to protocol non-adherence (eg, as randomized analysis), and any statistical methods to handle missing data (eg, multiple imputation)*

All trial data will be analyzed by biostatistician based at the University of Health Sciences, Lahore, using an a priori, approved analysis plan (SPSS 25.0). Interim analyses at each stage (first stage will be 10% of the total sample size) of the adaptive design will be pre-planned and undertaken confidentially keeping investigators and participants blind till the end of the trial. Primary and secondary outcomes will be analyzed in accordance to the group in which the participants were randomized deploying the intention-to-treat principle. The primary analysis will be expressed as odds ratio (OR) of the comparison between groups for the primary outcome. Interim analyses will be conducted without disclosing groups, thereby maintaining a level of blinding in interpretation of interim results. The confidential interim analyses at each stage of the adaptive design will examine for imbalance in co-morbidity at baseline. If any differences are observed then stratification may be modified confidentially. The results will be reported as point estimates and 95% confidence intervals. Secondary analysis will include in time-to-event data to directly compare the data among groups with survival plots and hazard ratios. This will permit evaluation of the decision to continue beyond Day 7 of treatment upon testing negative, potential drug effects besides informing valuable understanding of drug effectiveness. Stratified analyses will be done by baseline COVID-19 positive status upon testing and age groups. Multiple regression and Cox proportional hazards stratified analysis will be used to adjust for a small number of covariates taken from stratification factors if there were baseline imbalances. Secondary analyses will deploy multiple regression models as well Chi square, Fisher’s exact test and one-way ANOVA to compare groups. The two-sided p-value less than or equal to 0.05 will be taken as significant. Imputation method will be used to handle missing data.

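### The Outcomes section states the laboratory primary endpoint as time to a negative qRT-PCR, while the rest of the protocol defines, sizes and analyses it as negative at day 7

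*Protocol*

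**What the plan says.** Four parts of the protocol treat the laboratory primary outcome as status at one time point:

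- Abstract, Main Outcomes: "The laboratory-based primary outcome will be turning test negative for COVID-19 on qRT-PCR on day 7 of follow-up".
- Objectives, Primary Objective: viral clearance and clinical improvement are both assessed at day 7 and named as the primary outcomes.
- Sample size (SPIRIT item 14): about 520 per group, from 50% negative at day 7 on hydroxychloroquine against 60% in the comparator groups, 5% significance and 90% power.
- Statistical methods (SPIRIT item 20): the primary analysis is an odds ratio. Then: "Secondary analysis will include in time-to-event data to directly compare the data among groups with survival plots and hazard ratios".

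The Outcomes section (SPIRIT item 12) differs. It describes swabs on days 7 and 14 for "monitoring of primary endpoint - measuring time to turn test negative for COVID-19 on qRT-PCR", and adds that "those positive at day 7 will be followed up further till day 14 or beyond". Sample size also says: "Interim analysis will review sample size according to time to clearance also".

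Statistical methods adds stratified Cox regression to adjust for a few covariates if baseline imbalance appears. It does not name the event for the time-to-event analysis, and the protocol does not mention interval censoring or the handling of ties.

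**The concern.** Negative at day 7 and time to negative are different variables with different effect measures (odds ratio and hazard ratio). The Outcomes section is where a reader looks for the definition, and it gives the one that the trial was not sized on. The sample size sentence on time to clearance adds to the doubt, because no assumption about clearance times is given for such a review to check.

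The second matter is what the swabs can show. No swab is planned between baseline and day 7, so a clearance by then, expected in 50% to 60% of participants, is known only to lie in the interval (0,7]. If swab days are entered in a Cox model as exact event times, half or more of the participants share one tied time. The hazard ratio can then be pulled towards 1.

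**Working it through.** **1. Which endpoint was the trial sized on?** Inputs from Sample size: p1 = 0.50, p2 = 0.60, power 90%. Two-sided 5% is from Statistical methods. With pooled variance and mean proportion 0.55:

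n = [1.960·√(2·0.55·0.45) + 1.282·√(0.5·0.5 + 0.6·0.4)]² / 0.10² = (1.379 + 0.897)² / 0.01 = 518.04, rounded up to 519 per group.

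This agrees with the stated 520, at which power is 90.1%. The corresponding odds ratio is (0.6/0.4)/(0.5/0.5) = 1.50. No calculation for time to clearance is given.

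**2. The wording side by side.**

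| Place | Laboratory primary endpoint |
|---|---|
| Abstract | negative at day 7 |
| Primary Objective | at day 7 |
| Sample size, calculation | proportion negative at day 7 |
| Statistical methods | odds ratio; time-to-event is secondary |
| Outcomes | time to negative |

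Only the Outcomes section departs from the day-7 definition.

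**3. Cox on swab days, if the event is PCR clearance.** Assumptions that the documents do not state: proportional hazards; 75% or 90% of the reference arm clear by day 14; every clearance recorded at day 7 or 14; everyone else censored at day 14; no dropout. The constant-hazard case is the one with 75%.

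True hazard ratio = ln(0.40)/ln(0.50) = 1.322, log 0.2791.

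Expected counts with 520 per arm:

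- Day 7: 260 of 520 v 312 of 520 in both cases.
- Day 14, 75% case: the comparator has 0.25^1.322 = 0.16 uncleared. Events are 130 of 260 v 124.8 of 208.
- Day 14, 90% case: the comparator has 0.10^1.322 = 0.0477 uncleared. Events are 208 of 260 v 183.2 of 208.

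Breslow ties: solve Σd2 = Σ(d1 + d2)·r2θ/(r1 + r2θ), with d the events and r the numbers at risk at each swab day.

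- 75% case, θ = 1.20: day 7 gives 572·624/1144 = 312; day 14 gives 254.8·249.6/509.6 = 124.8. Both match the observed counts. The estimate is simply the ratio of interval risks, 0.6/0.5.
- 90% case, θ = 1.159: the two terms sum to 307.0 + 188.2 = 495.2, equal to 312 + 183.2.

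Efron ties were maximised numerically on the same counts.

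| Reference arm clear by day 14 | Breslow | log effect lost | Efron | log effect lost |
|---|---|---|---|---|
| 75% | 1.20 | 1 − 0.1823/0.2791 = 35% | 1.30 | 5% |
| 90% | 1.16 | 1 − 0.1473/0.2791 = 47% | 1.27 | 13% |

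A complementary log-log model on the intervals gives ln(−ln 0.40) − ln(−ln 0.50) = 0.2791 for the first interval and the same for the second, so it recovers 1.322 in both cases.

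**4. No true effect.** In 300 simulated trials of 520 v 520 with 50% clear by day 7 in each arm and constant hazards, both tie methods gave hazard ratios of about 1.00. They rejected in 0.7% (Breslow) and 4.0% (Efron) of trials.

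**The case against.** The Outcomes phrase sits in a sentence about swab collection, and everything else that matters for the primary analysis points to day 7: abstract, objective, sizing, odds ratio. Time-to-event is expressly secondary, and analysis is to follow a plan approved in advance. This stands as far as it goes. A reader might infer two rival primary endpoints with the choice left until the data are seen. The documents do not support that, since no primary time-to-event analysis is planned anywhere. What remains is a contradiction in the section that should fix the endpoint.

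On the model, the objection is stronger. The tie method is not stated and may be set in a statistical analysis plan that is not shown. With Efron ties the loss is 5% in the constant-hazard case. The day-14 clearance figures are assumed. The event is inferred: PCR clearance is likely because Statistical methods refers to testing negative, but the ordinal scale and mortality are also recorded over time. Cox regression is planned only for adjustment if there is imbalance. Follow-up beyond day 14 may add swabs, so it is too strong to say that swabs exist only on days 7 and 14. All of this limits the modelling point to a conditional one. It does not alter the absence of any planned swab between baseline and day 7.

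**Conclusion.** The contradiction is established from the text alone. The laboratory primary endpoint should read as negative at day 7, the definition on which the 520 per group rests (519 on recalculation).

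The modelling point holds in direction, with a size that depends on choices the protocol does not state. At the protocol's own day-7 rates, under proportional hazards and with 75% to 90% of the reference arm clear by day 14, 35% to 47% of the log hazard ratio is lost with Breslow ties and 5% to 13% with Efron ties. It applies only if the event is PCR clearance.

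A reader might infer that the trial's main result is distorted. It is not: the analysis concerned is secondary, the bias is towards no effect, the simulation showed no false effect under the null, and the day-7 odds ratio does not depend on swab spacing. Nor do the documents give grounds for dropping the survival plots. A curve that steps at swab days is coarse but not wrong.

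**What to change.** - **Outcomes:** state that the laboratory primary endpoint is qRT-PCR negative at day 7 (yes/no), and that later swabs support a secondary time-to-clearance analysis.
- **Sample size:** reconcile the time-to-clearance sentence with this, so that sample size review rests on the day-7 endpoint.
- **Statistical methods:** name the event for the time-to-event analysis. If it is PCR clearance, use a grouped-time (complementary log-log) or interval-censored model on the swab intervals: (0,7], (7,14], and later intervals where later swabs exist. Survival plots may stay, read as steps at swab days.

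The cost is protocol wording and a different model for one secondary analysis. It needs no extra swabs or participants, and the 520 per group is unchanged.

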***Methods: Participants, interventions, and outcomes***

**4 PARTICIPANTS**

***SPIRIT Guidance: Study setting***

*9 Description of study settings (eg, community clinic, academic hospital) and list of countries where data will be collected. Reference to where list of study sites can be obtained*

Study sites comprise major public-sector tertiary care health facilities and Covid-19 field hospitals being setup within province of Punjab. Hospitals in other provinces and federal areas will also be invited for participation. Households with self-isolating individuals could also participate in the study. A list of hospitals with confirmed participation has been attached as **Annex 3.**

***SPIRIT Guidance:*** *Eligibility criteria*

*10 Inclusion and exclusion criteria for participants. If applicable, eligibility criteria for study centers and individuals who will perform the interventions (eg, surgeons, psychotherapists)*

Eligible will be newly diagnosed patients without any comorbidities or those with controlled chronic medical conditions, e.g. diabetes mellitus and hypertension. Participants of either gender or age group having tested positive for COVID-19 on qRT-PCR (Quantitative Reverse Transcription PCR) will be invited to take part. Participants who are pregnant or lactating, are already taking any treatment, under respiratory distress or severely dyspneic, have liver and kidney failure will be excluded from the study. Each participant will undergo baseline investigation i.e., liver function tests, renal function tests, urinalysis, and Complete Blood Count; at the time of enrollment. However, diagnostic facilities and hospital admission criteria could vary across cities. A case report form (CRF) has been developed for this proposal and **attached** at the end of this document.

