***SPIRIT Guidance: Ancillary and post-trial care***

30 Provisions, if any, for ancillary and post-trial care, and for compensation to those who suffer harm from trial participation

The study is conducted in view of lack of treatment options for mild to moderately symptomatic SARS-Cov-2 with a commitment to no-harm practices and a robust adverse drug reaction monitoring framework.

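### The clinical primary outcome needs a baseline score that the written schedule for the scale does not list, and its two-point rule makes response impossible from the two best starting categories

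*Protocol*

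**What the plan says.** The protocol's Abstract (Main Outcomes) states: "The clinical primary outcome will be improvement from baseline of two points on a seven-category ordinal scale on day 7 of follow-up".

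The Outcomes section (SPIRIT item 12) is the only text shown that schedules this scale. Symptom change is to be "reported on the 7-point ordinal scale on each of days 3, 5, 7, 9, 11, and 14". The same section gives two secondary instruments a baseline: "Secondary outcomes like Quality of Life and Symptoms Score will be recorded on day 0 and 7". The eligibility text (SPIRIT items 9 and 10) lists what is done at enrolment: "Each participant will undergo baseline investigation i.e., liver function tests, renal function tests, urinalysis, and Complete Blood Count; at the time of enrollment". The ordinal scale is not in that list.

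On the population, the Abstract invites "newly diagnosed patients, either hospitalized or in self-isolation, without any comorbidities" or with controlled chronic conditions. The Inclusion Criteria require symptoms, and the Exclusion Criteria remove respiratory distress and severe dyspnea. SPIRIT item 30 refers to the "lack of treatment options for mild to moderately symptomatic SARS-Cov-2".

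The Sample size section (SPIRIT item 14) derives about 520 per group from 50% v 60% on the laboratory outcome, and says this also suffices for Cohen's d 0.3 on the clinical outcome. The Statistical methods section (SPIRIT item 20) names the odds ratio as the primary measure.

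**The concern.** There are two separate points.

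First, a change from baseline needs a baseline. The listed days for the scale start at day 3, and the authors do write day 0 where they list the secondary instruments. If sites followed only the written list, a primary outcome would lack its starting value, and no analysis method could supply a measurement that nobody took. Treatment is open-label, so a starting category reconstructed after allocation would also be open to bias.

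Second, the two-point rule has a ceiling. A patient one step from the best category who recovers completely counts as a failure, in whichever direction the scale is numbered. In a trial that excludes the sickest patients and admits self-isolating ones, this could apply to a material part of each arm.

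**Working it through.** **Schedule, side by side**

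| Item | Days given in the text |
|---|---|
| Ordinal scale (primary) | 3, 5, 7, 9, 11, 14 |
| Quality of life, symptom score (secondary) | 0, 7 |
| Laboratory tests | enrolment |
| Endpoint definition | baseline and 7 |

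The endpoint presupposes a baseline rating, and no text shown places one in the schedule.

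**Ceiling**

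Rank the categories from the best, k = 1 to 7. The largest possible gain is k − 1: 0 from the best, 1 from the second best, 2 from the third best, and so on. A two-point gain is impossible for k = 1 and k = 2 and possible for the other five.

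**The protocol's own figures**

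Inputs from the Sample size section: 50% v 60%, 5% significance (two-sided per the Statistical methods section), 90% power.

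n = [1.96·√(2·0.55·0.45) + 1.2816·√(0.25 + 0.24)]² / 0.10² = (1.379 + 0.897)² / 0.01 ≈ 518.04, rounded up to 519. The stated 520 reproduces.

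For d = 0.3: n = 2·(1.96 + 1.2816)² / 0.3² ≈ 234 per group, so 520 is ample for a difference in means (power 0.998). The defined endpoint, however, is a yes/no response.

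**Effect of fixed non-responders**

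Let f be the share starting in the two best categories, equal in all arms. The documents do not give f, so it is an assumption. If those able to respond have rates p1 and p2, the observed rates are (1 − f)p1 and (1 − f)p2. The risk ratio p2/p1 does not change. The risk difference is multiplied by (1 − f), and the odds ratio moves towards 1.

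Power = Φ[(|difference| − 1.96·SE0) / SE1], with SE0 from the pooled rate and SE1 from the separate rates, n = 520 per group.

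*Illustration A, the clinical effect size.* Assume d = 0.3 converts by the logistic rule: OR = exp(0.3·π/√3) ≈ 1.72. Assume also a 50% reference rate among those able to respond; the other arm is then 1.723/2.723 = 63.3%.

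Worked line at f = 25%: the rates are 37.5% and 47.5%, difference 0.0996, SE0 = 0.0307, SE1 = 0.0305. Power = Φ[(0.0996 − 0.0601)/0.0305] = Φ(1.30) ≈ 0.90.

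*Illustration B, the laboratory rates.* 50% v 60%, borrowed because the protocol gives no clinical response rates.

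| f | A: rates | A: OR | A: power | B: rates | B: OR | B: power |
|---|---|---|---|---|---|---|
| 0 | 50.0 v 63.3% | 1.72 | 0.99 | 50 v 60% | 1.50 | 0.90 |
| 10% | 45.0 v 57.0% | 1.62 | 0.97 | 45 v 54% | 1.44 | 0.83 |
| 25% | 37.5 v 47.5% | 1.51 | 0.90 | 37.5 v 45% | 1.36 | 0.69 |
| 50% | 25.0 v 31.6% | 1.39 | 0.66 | 25 v 30% | 1.29 | 0.44 |

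Illustration A depends on the reference rate: at f = 25%, power is 0.93 with a 30% reference and 0.83 with 60%.

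**The case against.** The endpoint definition itself presupposes a baseline rating, and the sentence listing days 3 to 14 reads naturally as a list of follow-up visits. The participant timeline (Figure 1) and the case report form are attached to the protocol but not shown here, and either may contain a day-0 score. This stands. A reader might infer that no baseline is collected and that the endpoint cannot be derived, or that day 3 would serve as baseline. The documents do not support either: what can be shown is an inconsistency between the outcome definition and the written schedule, and no text proposes day 3.

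On the ceiling, the seven categories are not defined in the text shown and there is no baseline distribution. The symptom requirement may leave the best category almost empty. The Recruitment section makes home recruitment conditional on pressure on the health system, although other sections allow it outright. So a statement that many patients start at the good end would be inference. The second-best category is affected all the same.

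On size, a reader might take the laboratory rates as the basis and conclude that power falls from 90% to 44% at f = 50%. Those rates belong to the other primary outcome. On the effect size that the protocol gives for the clinical outcome, the loss is smaller. Nor is the test biased: with equal f, the null hypothesis is tested validly.

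Finally, the choice of model, and even the handling of patients near the ceiling, could sit in a statistical analysis plan that is not shown. That is fair for the model. The two-point rule, however, is fixed in the protocol's outcome definition, and its ceiling follows from it.

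**Conclusion.** The point holds in two limited parts. The definition of the clinical primary outcome and the written schedule for its scale do not agree on a baseline rating and must be reconciled; whether the rating is in fact collected cannot be settled from the text shown. The two-point rule makes the two best starting categories fixed non-responders, which is exact for any seven-category scale.

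The cost is a smaller odds ratio, the stated primary measure, and lower power; validity of the test and the risk ratio are unaffected. Its size rests on the unknown f, on f being equal across arms, and on assumed response rates. On the clinical effect size with a 50% reference rate, the loss is slight at f = 10%, and power is still about 0.90 at f = 25%; it becomes serious at f = 50% (0.66). This should be fixed; confidence is moderate.

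**What to change.** Add an ordinal rating on day 0, before randomisation, to the schedule in the Outcomes section, and bring the timeline figure and case report form into line with it.

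Then, by amendment before any comparison by arm, choose one of these:

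- Analyse the day-7 category with an ordinal (proportional-odds) model adjusted for the day-0 category. The result is still an odds ratio, and the two-point response stays as a secondary summary.
- Define response as a gain of at least two points, or a move from the second-best to the best category. State that patients already in the best category at day 0 are not automatic responders. They remain unable to respond under this rule, so their number should be reported.

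The cost is one bedside or phone rating per patient, the amendment wording and, for the ordinal model, a check of the proportional-odds assumption. About 470 patients had been recruited by July 03, 2020. If no day-0 rating was taken, their starting category can be recovered only where contemporaneous records allow. Admission records will not serve home-isolated patients recruited by phone, so the gap should be stated as a limitation.
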